### Design

This 2 x 2 factorial cluster randomized controlled trial, called *MalTrials*, will be carried out for approximately 116 weeks from September 2014 to December 2016. The village (or cluster) will be the unit of randomization, and an equal number of villages will be randomized to one of the four arms: (1) LLINs + IRS, (2) LLINs alone, (3) IRS alone or (4) control (routine practice). The control arm will receive the routine standard practice of malaria prevention of the Ethiopian Malaria Control Program.

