#### Entomological study

We aim to calculate the sample size for the entomological collections based on the pilot entomological studies. In a West African study with a 90 % power and 5 % significance level, it was advised to sample eight houses from each of 15 clusters of the study arms, but the mosquito density was lower [56]. A total of 16 villages (four per arm) will be randomly selected for entomological study, in which indoor host-seeking mosquitoes will be collected by CDC light traps from four houses per arm, indoor resting mosquitoes from 16 houses per arm using pyrethrum spray collection and outdoor resting mosquitoes from four artificial pit shelters per arm of the study.

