#### Entomological data collections

The results of trials from countries where *An. gambiae* s.s. is the dominant vector might not be fully applicable in countries such as Ethiopia, where *An. arabiensis* is the main vector. The latter vector is less affected by mosquito nets, and is more exophilic and less anthropophilic [58]. Estimating the human biting rate (HBR) of mosquitoes is important for a risk assessment of malaria transmission. The Centers for Disease Control and Prevention (CDC) light traps, used in many studies, are only a proxy measure to estimate HBR. Human landing catches (HLC) are a more direct way to estimate HBR, and are often considered the “gold standard” [59]. Recent research showed that light trap collections placed close to inhabited mosquito nets may not be a reliable method of assessing human biting rates [60].

The CDC light traps and HLC will be compared before starting the trial. Since HLC cannot be used for community-wide mosquito collections due to ethical and logistical drawbacks, CDC light trap collections will be calibrated with HLC locally in order to estimate an operational conversion factor for calculating the HBR and EIRs. Mosquito collections will be carried out during the malaria transmission season following interventions.

The CDC light traps, pyrethrum spray sheet catches and artificial pit shelters will be employed to collect mosquitoes and assess their biting behavior, indoor and outdoor resting densities. Houses will be randomly selected from a computer-generated list and the person will be blinded to the arms and houses. For CDC light traps and pyrethrum spray catches, the number of houses will be four and 16 from each arm, respectively, while four pit shelters in each arm will be constructed. Mosquitoes will be collected weekly from August to November each year, and will be identified to species using a morphological key [61]. Previous studies indicated the presence of *An. arabiensis* as the only species of the *An. gambiae* complex in the study area [50]; however, for reconfirmation purpose a species-specific polymerase chain reaction (PCR) will be applied [62].

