The WHO age-adjusted cut-off for Hb will be used to classify anemia in children [71]. For children between 6–59 months of age, a normal Hb level is defined as Hb of 11.0 g/dl or greater and as mild at 10.0–10.9 g/dl. Moderate anemia is defined as children with an Hb level of 8.0–10.9 g/dl while severe anemia is defined as an Hb level of less than 8.0 g/dl. At a community level, a prevalence of anemia will be stated to be severe if over 40 % of the children are anemic (combining mild, moderate and severe) and moderate if the prevalence is 20–39.9 %. We will measure the weight and height of all children under the age of 5 years, and calculate the anthropometric indices such as weight for height, height for age, and weight for age. Both malaria and anemia prevalence data will be compared in the intervention and control clusters using multilevel mixed-effects logistic regression models, taking clustering effects into account.

Cost-effectiveness, expressed as an incremental cost-effectiveness ratio (ICER), will be calculated for each outcome and arm using standard DALY weights. The interventions will be ranked according to cost-effectiveness, whereas inequality in terms of health outcomes, will be measured by the Gini coefficient and the concentration index [72].

The agreement between the two mosquito collection methods, HLC and light traps, in assessing mosquito sampling efficiency will be calculated by a parametric approach based on an analysis of variance and simple graphical methods. Indoor and outdoor *Anopheles* densities will be compared among the study arms using a one-way analysis of variance (ANOVA) if data are normally distributed or using a Mann-Whitney *U* test if data are non-normally distributed.

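### Mosquito densities are to be compared by one-way ANOVA or Mann-Whitney U with no allowance for village, although only four randomised villages per arm are sampled, week after week

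*Protocol article*

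**What the plan says.** Under Design, "The village (or cluster) will be the unit of randomization". Under Sample size, Entomological study, "A total of 16 villages (four per arm) will be randomly selected for entomological study". Host-seeking mosquitoes are "collected by CDC light traps from four houses per arm, indoor resting mosquitoes from 16 houses per arm using pyrethrum spray collection". For the outdoor catches, each arm has four pit shelters. Entomological data collections repeats the house counts and sets the frequency: "Mosquitoes will be collected weekly from August to November each year".

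Study endpoints lists two secondary entomological measures: the mean number of *An. arabiensis* per light trap per night, and the mean number in spray catches per night. EIR is the primary entomological measure.

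The Analytical plan then states that indoor and outdoor densities "will be compared among the study arms using a one-way analysis of variance (ANOVA) if data are normally distributed", with Mann-Whitney U for non-normal data. It mentions no term for village, house or week and no village-level summary. Earlier in the same section, malaria and anemia prevalence are to be compared "using multilevel mixed-effects logistic regression models, taking clustering effects into account".

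**The concern.** Both tests assume independent observations. Catches from one village share its distance from breeding sites, its housing and its livestock, so they resemble each other more than catches from different villages. The protocol itself says that swampy areas of Lake Zeway contribute strongly to mosquito breeding, so real differences in density between villages are to be expected under any allocation. With four villages per arm, such differences need not balance out. A catch-level test takes its error term mainly from night-to-night variation and so understates the uncertainty of a comparison between arms.

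At stake is a stated secondary objective (whether the combination lowers entomological parameters, resting density among them) and one of the research questions in the abstract, on vector density. A density difference due to village location could be credited to the combined intervention.

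There is a second mismatch. The sentence promises a comparison among the study arms, of which there are four. One-way ANOVA does that. Mann-Whitney U compares two groups, and the plan does not say which pairs would be tested.

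**Working it through.** The protocol gives no power, sample-size result or error rate for the density comparison, so there is no figure to reproduce. The check asks how often the named tests reject when no arm differs.

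**Inputs from the protocol.** Four arms; four villages per arm; four light-trap houses, 16 spray-catch houses and four pit shelters per arm; weekly collection from August to November.

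**Derived.** August to November is 122 days, and 122/7 is about 17 weeks. Light traps and pits: 4/4 = 1 per village on average, so m = 17 catches per village per season. Spray catches: 16/4 = 4 houses per village, so m = 4 × 17 = 68. An even spread over villages is an assumption.

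**Assumed.** ICC of 0.01, 0.05 and 0.10 (none is given for mosquito density), and a 5% test level, which the protocol states only for malaria incidence.

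**Catch-level ANOVA, m = 17.** Total catches N = 4 × 4 × 17 = 272, so the F test uses 3 and 268 df, with critical value 2.64. Set total variance to 1.
- Expected arm mean square: (1 − ICC) + m × ICC = 1 + (m − 1) × ICC, the design effect. This is 1.16, 1.80 and 2.60 at the three ICCs.
- Expected residual mean square, pooling 12 village df and 256 within-village df: [12 × design effect + 256 × (1 − ICC)]/268. At ICC 0.10 this is (31.2 + 230.4)/268 = 0.976.
- The F ratio is therefore inflated by about 2.60/0.976 = 2.66 at ICC 0.10, 1.80/0.988 = 1.82 at 0.05 and 1.16/0.998 = 1.16 at 0.01.
- Hand check at ICC 0.10: rejection needs a chi-square on 3 df above 3 × 2.64/2.66 = 2.97, which has probability of about 40%.

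Sampling from the nested-ANOVA components (200,000 draws) gives:

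| Catches per village | ICC 0 | ICC 0.01 | ICC 0.05 | ICC 0.10 |
|---|---|---|---|---|
| 17 (light trap or pit, one season) | 5% | 8% | 23% | 40% |
| 68 (spray catch, one season) | 5% | 20% | 62% | 80% |
| ANOVA on 16 village means (3 and 12 df) | 5% | 5% | 5% | 5% |

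A separate simulation of individual catches gave 9% at ICC 0.01 with m = 17, hence 8 to 9%.

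**One pairwise Mann-Whitney, m = 17.** Simulation gives about 6 to 7%, 13 to 14% and 21 to 24% at the three ICCs, over separate runs.

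**Counts instead of normal data.** Negative binomial catches (assumed mean 2 or 5, dispersion 0.5) with a between-village coefficient of variation of 0.27 give 13% for ANOVA and 8 to 9% for one Mann-Whitney at m = 17, and 44 to 45% and 19 to 20% at m = 68. The 0.27 is the protocol's value for malaria incidence, borrowed for illustration only.

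**Shared week-to-week variation.** All arms are sampled in the same weeks, so a common week effect adds to the residual but not to the difference between arms. If week is half the total variance (assumed), the ANOVA rates at m = 17 fall to about 1 to 2%, 13 to 14% and 32 to 33%.

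**Mann-Whitney on village means.** With four against four there are 70 arrangements, so the smallest two-sided exact p is 2/70 = 0.029. Bonferroni thresholds of 0.05/2 = 0.025 for two contrasts, or 0.05/6 = 0.0083 for all six pairs, cannot be reached.

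**The case against.** The strongest reply is that the unit of analysis is nowhere stated. The sentence speaks of densities, the endpoints are worded as means, and an analysis plan that is not shown may specify one mean per village. ANOVA on such means is valid. This stands: a reader might infer that the protocol commits to treating each catch as independent, and it does not say so. What remains is that it names tests whose validity depends on a unit it leaves open, beside outcomes defined per trap-night and per spray-catch night. It also leaves Mann-Whitney as the fallback for four arms.

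A second reply is that the Analytical plan elsewhere promises to consider village clustering and to include time as a fixed effect. That text follows the malaria-incidence models and lists person-level terms (repeated measurements in an individual, age, gender, net use). Neither named test can carry those terms.

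Third, the size is uncertain. The ICCs are assumed. Ignoring week does not itself create false positives; shared seasonality makes the tests conservative, and at ICC 0.01 it can outweigh the clustering. A reader might also pool three full seasons, 51 nights, and quote 73% at ICC 0.10. The nets were handed out on 1 to 5 October 2014, and collections are described as following the interventions. The first season then leaves about 8 weeks, so the total is about 8 + 17 + 17 = 42 nights, which gives 68%.

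Fourth, Mann-Whitney need not mean six unadjusted tests. The objective compares the combination with each single intervention, which is two contrasts. That is fair, but the sentence does not name them.

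**Conclusion.** The point holds in this form. The plan names tests with no allowance for village in a village-randomised design with four sampled villages per arm, and does not restrict them to village summaries. Applied to single catches, they reject too often: about 8 to 9%, 23% and 40% for light traps over one season at ICC 0.01, 0.05 and 0.10, and more for spray catches. These figures rest on assumed ICCs, an even spread of traps over villages and no shared week effect. With week at half the variance, the excess disappears at ICC 0.01 but remains at 0.05 and above. The supportable wording is that chance differences will too often look significant, not that they will look significant.

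The scope is the density comparisons: the two secondary entomological outcomes, and outdoor density. A reader might extend the criticism to all entomology, but the sentence does not cover EIR, and the malaria incidence outcome is untouched. It should be fixed, but it does not threaten the trial's main conclusion.

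**What to change.** Replace the sentence with a village-level analysis, in one of two forms:

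- ANOVA or a permutation test on the 16 village means (12 residual df); or
- a negative binomial mixed model of nightly counts with fixed effects for arm, week and season, a random effect for village, and small-sample inference on about 12 df.

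Add a random effect for house only for spray catches, and only if the same houses are resampled, which the protocol does not state. With one light-trap house per village, village and house effects cannot be separated.

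Replace Mann-Whitney U with a four-arm permutation or Kruskal-Wallis test on village means, or with pre-stated contrasts of the combination against each single intervention. Take such contrasts from the ANOVA or mixed model: a rank test of four villages against four cannot go below p = 0.029.

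The cost is analysis wording only; no new data are needed. The drawback is wider intervals, which is what four villages per arm can support.

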### Ethical considerations

#### Ethical approval

The study was approved by the IRB of the College of Health Sciences at Addis Ababa University, the Ministry of Science and Technology in Ethiopia (ref: 3.10/446/06) and the Regional Committee for Medical and Health Research Ethics, Western Norway (ref: 2013/986/REK Vest). The protocol was registered online on 8 September 2014 at the Pan African Clinical Trials Registry under the registration number PACTR201411000882128.

#### Community consultation and sensitization

Prior to the implementation of interventions, a consultative workshop and several meetings were held to explain the objectives, *kebele* selection and randomization, implementation procedures and expected outcomes of the trial to the communities with representatives from the ORHB, the East Shewa Zone Health Department and the Adami Tulu District Administration. Permission through official letters was obtained from various administrative levels. Study communities were sensitized prior to randomization through meetings and discussions with community leaders, *kebeles* and village leaders and community elders.

#### Information and informed consent

Verbal informed consent to participate in the study was obtained beforehand from the study participants and from parents/guardians for children under 18 years of age using the local *Afan* Oromo language. Information sheets were provided to inform about the purpose of the study, and the participants were informed that involvement in the study was voluntary and that they had the right to withdraw at any time regardless of reason. At each data collection, the verbal consent of the study participants and verbal assent from the parents/guardians for children were obtained using the local language. Assurance was also given that a refusal to participate in this study would not affect their access to services at the health posts in the study villages in the community.

#### Adverse events and malaria treatment

We do not anticipate any physical harm or risks to the participants. Blood samples for RDTs, microscopic examination of slides and Hb measurements will be collected using aseptically disposable lancets. A finger-prick for blood sample collection may result in mild pain and bruising at the site where blood is obtained, but will not cause any further harm. The collection of blood samples from finger-pricks is part of the routine procedures in the diagnosis of malaria by health workers. Malaria treatment will be provided according to the national guidelines using AL and chloroquine, which are the first-line antimalarial treatments for *P. falciparum* and *P. vivax*, respectively [43]. All study participants visiting health posts will be examined and treated for malaria free of charge, while the mass distribution of LLINs and IRS spraying will be carried out by the *MalTrials* project for free in collaboration with the DHO. Mosquito collectors will be trained to collect mosquitoes as soon the mosquitoes land and before they bite. To help minimize risk, data collectors will be provided with an appropriate prophylactic drug (Malarone) before the collections.

#### Confidentiality of information

To the best of our ability, all information from the study households and participants will be held in confidence and appropriate measures will be taken to ensure the confidentiality of information both during and after data collection. Access to information will be limited to data collectors, including health workers and their supervisors at sites of collection, data entry clerks and to the research team.

#### Trial oversight

There is no need for a Data Safety and Monitoring Board (DSMB) for this trial since all interventions, blood sample collection and treatments are part of routine malaria control in Ethiopia and will be undertaken in collaboration with the health workers at the health posts and the DHO. We do not foresee any adverse effects from the interventions, so we do not intend to apply any stopping rules for this trial. No participant in the control group will be impeded from obtaining mosquito nets from other sources, and malaria incidence in the control villages will be monitored throughout the study for possible case build-up or an outbreak of malaria. If the control villages encounter any malaria outbreaks, an intervention will be taken by the *MalTrials* project and the DHO in accordance with the national guidelines regardless of the trial.

Deltamethrin-treated LLINs and propoxur IRS are WHO recommended and meet the specifications of the WHO’s Pesticide Evaluation Scheme, and our interventions will follow the WHO and national recommendations [44, 73]. The hazard which may be associated with this trial is that the insecticides used for the IRS could leak into the environment. Empty sachets, cartons, plastic bags, used gloves, pricking needles and other contaminated materials will be handled properly until they are finally burned. Lastly, all needle safety procedures will be in line with WHO standard.

### Timelines of activities

The trial is being carried out for a period of approximately 116 weeks from September 2014 to December 2016, with Table 1 showing details of the timetable of activities.

**Table 1 Tab1:** Timetable of activities

Activity by year and month	J	F	M	A	M	J	J	A	S	O	N	D
2013												
Ethical approval		x	x	x	x	x	x	x	x	x		
Development of data collection tools					x	x	x	x	x	x	x	x
Census and mapping			x	x								
Epidemiological pilot study									x	x	x	x
Entomological pilot study						x	x	x	x	x	x	
2014												
Selection of clusters		x	x	x	x							
Randomization of study clusters						x						
Procurement of LLINs			x	x	x	x	x	x				
Procurement of insecticide				x	x	x						
Household numbering and tagging						x	x					
Baseline data collection							x	x				
LLINs distribution									x	x		
Protocol registration								x	x			
IRS spraying									x			
LLINs distribution									x			
PCD and weekly household visit									x	x	x	x
Entomological surveys							x	x	x	x	x	
Cost data collection									x	x	x	x
2015												
Anemia survey	x											
Malaria prevalence survey									x	x	x	
PCD and weekly household visit	x	x	x	x	x	x	x	x	x	x	x	x
Entomology lab assays and field surveys	x	x	x	x	x	x	x	x	x	x	x	x
Cost data collection	x	x	x	x	x	x	x	x	x	x	x	x
IRS spraying and LLINs’ replacement								x				
Data entry and cleaning	x	x	x	x	x	x	x	x	x	x	x	x
Sensitization of study population								x	x	x		
2016												
Anemia survey	x											x
Malaria prevalence survey									x	x	x	
PCD and weekly household visit	x	x	x	x	x	x	x	x	x	x	x	x
Entomology lab assays and field surveys	x	x	x	x	x	x	x	x	x	x	x	x
Cost data collection	x	x	x	x	x	x	x	x	x	x	x	x
IRS spraying and LLINs’ replacement								x				
Data entry, cleaning and analysis	x	x	x	x	x	x	x	x	x	x	x	x
Entomological lab assays and field surveys	x	x	x	x	x	x	x	x	x	x	x	x
Cost-effectiveness analysis	x	x	x	x	x	x	x	x	x	x	x	x
2017												
Dissemination of findings to the study community	x	x										
Data analysis and report writing	x	x	x	x	x	x						
Scientific writing and publications	x	x	x	x	x	x	x	x	x	x	x	x
Final report to the funding agency				x	x	x						
Dissemination of findings to stakeholders							x					

*LLINs* long-lasting insecticidal nets, *PCD* passive case detection

## Discussion

In an effort to accelerate the reduction and ultimate elimination of malaria, IRS with insecticide and the universal distribution of LLINs have been implemented in recent years in many countries in SSA. It is well-accepted that decisions regarding malaria interventions should be based on robust evidence of the benefits and cost-effectiveness of the interventions. Since the rollout of both interventions requires considerable resources, there is an urgent need to evaluate additional protective benefits and the cost-effectiveness of the combination of the interventions. This study aims to measure whether IRS in combination with LLINs increases protection against malaria incidence compared to the use of LLINs alone, IRS alone or current routine practices. The intervention will consist of four “arms”: LLINs + IRS, LLINs alone, IRS alone and control (routine practice).

The main outcome of the trial will be the assessment of the incidence of malaria using PCD at health posts. Our sample size is relatively large compared to other trials, e.g., a study in the Gambia used 35 clusters of 110 children in each of two arms to detect a 50 % reduction in the incidence of malaria [56]. Our preliminary sample size calculations based on malaria incidence rates in southern Ethiopia [60] showed that we might need to include 10 clusters per arm with approximately 50 households (250 persons) per cluster. However, a Cochrane review advocates large-sized clusters [8].

Conducting research to evaluate the impact of community interventions raises a number of practical issues [21]. Both LLINs and IRS interventions are implemented by the project, and we anticipate that the coverage of the interventions will be very high despite issues of net use and the re-plastering of sprayed walls of the houses. We understand that the recent relatively low incidence of malaria in the area will have an impact on the proper and consistent use of LLINs by the community, which may challenge an active participation by the community. We will monitor LLINs ownership and use by household members on a weekly basis, and we will also assess the magnitude of the re-plastering rates of houses and teach the community about its consequences on malaria.

Some of the strengths of our study are that we have carried out extensive pilot studies before starting the trial. This enabled us to estimate the variance in malaria incidence among the villages and thus the sample size. In the previous published trials, the IRS insecticide was bendiocarb which has a relatively short residual duration on the walls, or DDT, against which the insecticide resistance has become widespread [38–42]. The current trial evaluates the added protection of propoxur, which has a relatively longer duration on walls compared to DDT. In addition, we also determined that the anopheline vectors in the study area are susceptible to propoxur. One of the limitations of this trial is that the communities will not be masked or blinded to the intervention. This would create a bias towards an increased effect of the combined intervention compared with other arms of the trial. This trial will not use a buffer zone between clusters of the different interventions as it will be carried out in rural areas with scattered households. As a result, the proximity of the clusters may influence the results. However, this applies to only some of the selected villages that are close to each other. As the positions of all households are recorded, we shall also try to adjust for possible close proximity of the villages during analysis.

The community in the “routine practice” with a weekly follow-up is in a better position than the community in the “routine practice” without any follow-up. Therefore, we decided to allow the trial with all four arms and emphasized that every participant will have access to weekly visits by the *MalTrials* project field personnel, early diagnosis and state of the art treatment for malaria. Adami Tullu was one of the 19 IRS targeted districts of the President’s Malaria Initiative (PMI) and the Ministry of Health (MOH) between 2008 and 2013 [74]. However, since 2014 the PMI has shifted its target areas to other districts in the Oromia Region. However, we will continuously monitor all groups including the control arm of the study if unforeseen malaria epidemics should arise.

This study is proposed at a time of significant need within the countries of SSA on how to effectively use IRS and LLINs interventions for malaria control and elimination. Consequently, the study is well-timed to assess whether the combination of LLINs and IRS could contribute towards the elimination of malaria. The trial addresses how to promote the uptake of research findings into public health programs by enhancing the knowledge base on interventions that will improve the effectiveness and coverage of anti-malaria interventions.

This study is expected to generate important evidence to inform the malaria control programs and the public regarding the effectiveness and cost-effectiveness of the two major vector control interventions. The costs of our intervention is similar to that of the existing malaria control program so that they can be easily accepted by the MOH. We anticipate that the findings of this study will be used for an effective planning and implementation of vector control interventions.

